### Outcomes

We will measure the following endpoints in all four arms. The primary endpoint will be the case notification rate in the intervention and control ODs during the study period. We define a TB case to be either bacteriologically confirmed (smear-positive identified by smear microscopy, culture, or rapid diagnostics approved by the World Health Organization (WHO)), smear-negative TB (two sputum samples tested negative and clinically diagnosed by a clinician—with abnormal CXR or no improvement in response to a course of broad-spectrum antibiotics), or extrapulmonary TB (presence of local symptoms such as enlarged lymph nodes, joint swelling, and Gibbus deformity and presence of general symptoms such as cough, fever, weight loss, and night sweats) [23]. This will be ascertained from the results of the screening and routine case notification data reported to the NTP. We will also determine: additionality, comparing the yield in each arm with its respective historical baseline (same period in the preceding year); and cumulative yield over the project implementation period. Secondary endpoints will include: the number of people needed to screen to detect one TB case; direct and indirect costs per TB case notified; and the treatment outcome of all people with TB in this study. These data will be collected on the aggregated form at the health center level or as reported by the project implementation team in each arm, except cost data, which will be collected from study participants in the baseline and follow-up surveys.

### Participant timeline

The participant timeline is presented in Table 1.

**Table 1 Tab1:** Schedule of enrollment, implementation of interventions, assessments, and data collection for the period of the trial

Timepoint	Study period								
	Enrollment	Allocation	Post-allocation						
	2019	2019	2019	2020	2020	2020	2020	2021	2021
	Q3	Q3	Q4	Q1	Q2	Q3	Q4	Q1	Q2
Enrollment (cluster level)									
Assessment of cluster	X								
Randomization of cluster	X								
Allocation of intervention		X							
Interventions									
Active case finding with a seed-and-recruit model			X	X	X	X	X		
Active case finding targeting household and neighborhood contacts			X	X	X	X	X		
Active case finding targeting people aged 55 years and older using mobile screening units			X	X	X	X	X		
Passive case finding			X	X	X	X	X		
Assessments (cluster level)									
TB case notification by selected clusters			X	X	X	X	X		
TB cases reported by each arm			X	X	X	X	X		
Individuals screened for TB			X	X	X	X	X		
Treatment outcomes					X	X	X	X	X
Cost data			X	X	X	X	X	X	X
Assessments (individual level)									
Enrollment			X	X	X	X	X		
Baseline survey			X	X	X	X	X		
Follow-up survey					X	X	X	X	X

*TB* tuberculosis, *Q* quarter

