**Methods:**

This pragmatic cluster randomized controlled trial will be conducted between December 2019 and June 2021. We will randomize eight operational districts (clusters) in seven provinces (Kampong Cham, Kampong Thom, Prey Veng, Thbong Khmum, Kampong Chhnang, Kandal, and Kampong Speu) to either the control group (PCF) or the intervention groups (ACF using a seed-and-recruit model, ACF targeting household and neighborhood contacts, and ACF targeting persons aged ≥ 55 years using mobile screening units). The primary endpoints will be TB case notification rates, additionality, and cumulative yield of TB cases. The secondary endpoints include treatment outcomes, the number needed to screen to find one TB case, and cost-effectiveness outcome measures. We will analyze the primary and secondary endpoints by intention to treat. We will compare cluster and individual-level characteristics using Student’s *t* test and hierarchical or mixed-effect models to estimate the ratio of these means. The incremental cost-effectiveness ratio per disability-adjusted life year averted will also be considered as a benchmark to determine whether the interventions are cost-effective.

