##### Intervention 3: ACF targeting the older population (people aged ≥ 55 years) using mobile screening units

In the intervention clusters (Fig. 4), an outreach team will conduct training and sensitization of the target population prior to the screening session. We will set up a screening site at a designated time, day, and place. Communities in the districts will be informed of the schedule for a one-off mass screening session before the screening day. Each person who visits the screening session will be screened and surveyed at registration by trained staff. Information on their age, demographics, and presence of TB symptoms will be collected. CXR will then be performed on-site for all persons exhibiting TB symptoms, and all individuals aged ≥ 55 years regardless of symptoms. CXR will be assessed by trained CXR readers on-site. When features suggestive of TB are found, sputum samples will be collected for GeneXpert testing on-site as well. Test results will be communicated to the participants immediately or via telephone calls, and people with TB will be referred for treatment and follow-up at the health center where screening is conducted or a health center of their choice. TB treatment and care at the health center will be provided according to the guidelines of the NTP. Should the health center of their choice not fall within the selected sites, follow-up will be conducted via telephone calls. Cases suspected for extrapulmonary TB will be referred to the referral hospital for further assessment and diagnosis. A follow-up will be conducted 6 months from treatment initiation. The standard operating protocol of mobile screening sessions depicts that the intervention will only be conducted at the selected sites once in 1–3 years.

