### Statistical methods

#### Statistical methods for primary and secondary outcomes

For the primary endpoints, we will compute TB case notification at the cluster level by dividing the total number of TB cases (all forms) notified by the selected ODs by the total population in each OD. Case notification rates will be presented as TB cases notified per 100,000 population per year. The difference in the total number of TB cases notified during the intervention period and the number of TB cases notified in the preceding 3 years will be computed to determine additionality. We will calculate the cumulative yield of TB cases by dividing the number of cases notified in each arm by the total number of people screened for TB. Cumulative yield will be presented as TB cases notified per 1000 individuals screened.

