## Trial status

Protocol version 1, December 3, 2019. Recruitment began on December 18, 2019 and will be completed by approximately December 31, 2020.

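### Notification counting is scheduled to end in the quarter ACF ends, so cases brought forward from 2021 count as additional with no later deficit, although the trial runs to June 2021

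*Protocol article*

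**What the plan says.** Table 1 (Participant timeline) marks the three ACF interventions, for example "Active case finding with a seed-and-recruit model", in Q4 2019 to Q4 2020. It marks "TB case notification by selected clusters" and the row for cases reported by each arm in exactly the same quarters. Treatment outcomes, cost data and the follow-up survey continue into Q1 and Q2 2021.

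The abstract states: "This pragmatic cluster randomized controlled trial will be conducted between December 2019 and June 2021". Under Trial status: "Recruitment began on December 18, 2019 and will be completed by approximately December 31, 2020".

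Outcomes words the endpoint more loosely: "The primary endpoint will be the case notification rate in the intervention and control ODs during the study period". On the data source it adds: "This will be ascertained from the results of the screening and routine case notification data reported to the NTP". The statistical methods define additionality more narrowly, against a historical period whose length is given in years: "The difference in the total number of TB cases notified during the intervention period and the number of TB cases notified in the preceding 3". The same section divides the cost difference between arms by the difference in TB cases detected to obtain the ICER.

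The household and neighborhood arm uses a one-off session at each health center. For the mobile-unit arm, "the intervention will only be conducted at the selected sites once in 1–3 years". The auditing section describes the KHANA arms as spread over one year. Since the other two ACF models are one-off, this fits the seed-and-recruit arm.

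**The concern.** ACF can raise notifications in two ways: by finding people who would never have been notified, and by finding sooner people who would have presented later. Both have value, but they answer different questions. The rationale rests on the first, the roughly 40% of cases in Cambodia said to go undetected.

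If counting stops when case finding stops, a person found in autumn 2020 who would have self-presented in spring 2021 adds one case to the ACF district, and the matching absence in 2021 is not recorded. The control arm borrows nothing from the future in this way. Randomization does not remove the asymmetry, because the intervention and the cut-off together create it.

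At stake are the notification-rate comparison, additionality and the ICER per case. Comparisons among the ACF arms are also affected, because the share of brought-forward cases that crosses the cut-off depends on when in the year each arm finds them.

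**Working it through.** **1. Calendar.** In Table 1 the ACF and notification rows cover the same five quarters, so no quarter of notification counting is scheduled after ACF ends. From 18 December 2019 to 31 December 2020 is T = 12.45 months. From then to 30 June 2021 is X = 5.95 months, with routine notifications still being produced.

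**2. What the cut-off does to a stated excess.** The document gives no share of cases brought forward, so this share is assumed. Take a control rate of 100 cases per 12 months and an in-window excess e. Let f be the share of that excess that would otherwise have been notified in the next six months. The 18-month gain is [(1 + e) + 0.5 − f·e]/1.5 − 1. With e = 0.30, one of the planning figures under Sample size:

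| f | ACF cases, 18 months | Control cases, 18 months | 18-month gain | 12-month window shows |
|---|---|---|---|---|
| 0 | 130 + 50 = 180 | 150 | +20% | +30% |
| 0.5 | 130 + 35 = 165 | 150 | +10% | +30% |
| 1 | 130 + 20 = 150 | 150 | 0% | +30% |

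The step from +30% to +20% is dilution: six months without ACF are added to the denominator. Only the fall below +20% is displacement.

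With e = 0.98 (the KHANA planning figure), f = 0 gives (198 + 50)/150 = 1.65 and f = 0.25 gives (198 + 50 − 24.5)/150 = 1.49. Here f cannot exceed about one half, because only 50 cases would be expected in those six months against an excess of 98.

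**3. Direction for the ICER.** For a cost difference C and 30 counted extra cases, the ICER is C/30. If 15 of the 30 were brought forward, the net figure is C/15. Counting displaced cases makes the ICER too low, which favors ACF.

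**4. Which arms are most exposed.** Assume an exponential lead time with mean m months. The share of brought-forward cases that would have been notified after the window closes is (m/T)(1 − exp(−T/m)) for case finding spread evenly over the window, and exp(−(T − s)/m) for a single session at month s. Of those crossing, 1 − exp(−X/m) would fall before the end of June 2021.

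| Mean lead time (assumed) | Spread over the year | Session at month 3 | Session at month 9 | Recovered by counting to June 2021 |
|---|---|---|---|---|
| 3 months | 24% | 4% | 32% | 86% |
| 6 months | 42% | 21% | 56% | 63% |
| 12 months | 62% | 46% | 75% | 39% |

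Cases brought forward within the window cancel, so an early session is affected least, and least of all when lead times are short.

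**The case against.** The strongest reply is that Outcomes sets the rate over the study period, and Table 1's study-period header spans columns to Q2 2021. On that reading the window might already reach June 2021. This stands as far as the wording is loose: a flat statement that counting stops in December 2020 goes beyond what Outcomes says. But nothing schedules notification collection after Q4 2020, and additionality is tied to the intervention period, so the wording does not cure the problem.

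Second, earlier diagnosis is itself an intended benefit, and the stated aim is more diagnoses and notifications. That is correct, and it is why the intervention-period rate can remain primary.

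Third, a secondary analysis is the kind of detail an article may leave to an analysis plan. The point here is the collection schedule and the additionality definition that the article does fix.

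Three stronger readings are tempting, and the documents do not support them:

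- A reader might infer that no arm can show a later dip. Sessions in two arms are one-off and their dates are not given, so post-session months may already be counted there.
- A reader might take the whole fall from +30% to 0% as bias. The first ten points are dilution, and f = 1 sits badly with a large undetected share.
- A reader might attach the 30% to the mobile units. The article attributes it to CENAT and does not say which organization runs which arm.

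**Conclusion.** The point holds as a limitation of the scheduled window. ACF cases that would otherwise have been notified after December 2020 count as additional with no offsetting deficit. This can inflate the rate comparison and additionality and, if its case count uses the same window, make the ICER per case too low. Exposure is greatest for the year-long seed-and-recruit arm and late one-off sessions, and smaller for early ones.

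The size cannot be derived from the documents, which give no lead time, no share brought forward and no session dates; the figures above are assumption ranges. Nor do the documents show that ACF merely shifts dates. They show only that the planned window cannot fully tell earlier detection from added detection. This does not invalidate the primary comparison, but it should be corrected because the means lie within the existing trial period.

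**What to change.** 1. State one counting window for the primary endpoint, reconciling Outcomes with Table 1 and the additionality definition. Keep the intervention-period rate as primary.
2. Extend the notification row of Table 1 to Q1–Q2 2021 for all eight districts.
3. Pre-specify a secondary analysis of cumulative notifications from intervention start to 30 June 2021, compared between arms and with the same calendar months wholly before the intervention. December 2017 to June 2019 would serve and lies within the three years of historical data already planned. The preceding-year baseline in Outcomes would not serve, because January–June 2020 falls inside the intervention period.
4. Report session dates by district, so that the months of counting after each session are visible.

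The cost is a small extra extract of routine data, with no new visits or consent. The net effect may come out smaller. Six months corrects only part of the displacement if lead times are longer. Nothing commits districts to remain free of ACF in 2021, and selection required freedom from ACF only currently and in the six months before implementation. Any ACF in 2021 or in the baseline months could therefore distort the comparison and should be recorded and reported.

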### Sample size

Simulations were conducted to estimate the power of the trial to detect a statistically significant difference between the intervention arms and the control arm for the primary outcome of the trial. To develop a basis for these simulations, we examined the ranges and variability of effect sizes from previously collected data that included operations data from CATA, CENAT, KHANA, and the NTP annual TB report 2018 [28]. We defined effect size as the percentage increase in the number of cases notified to the NTP because of the intervention (baseline: PCF). CATA, CENAT, and KHANA have implemented the respective interventions (different strategies of ACF) at different sites in Cambodia between 2017 and 2018. The percentage of estimated additional cases notified to the NTP by CATA, KHANA, and CENAT during the intervention period (scenario 1) was 110%, 98%, and 30%, respectively. For this scenario, the power was over 90%. We also considered three more sets of conservative effect sizes: (scenario 2) assuming all intervention arms have an effect size of 75%; (scenario 3) assuming all intervention arms have an effect size of 50%; and (scenario 4) assuming all intervention arms have an effect size of 25%. There was a similar level of power for a more cautious estimate (scenario 2—a 75% improvement in case notification). In scenarios 3 and 4, the power was maintained above 70% that a difference between intervention and control arms could be detected.

### Recruitment

The trial will be conducted at the selected ODs, and all communities and individuals who are eligible will be invited to participate in the activities.

### Assignment of interventions: allocation

#### Sequence generation

The unit of randomization will be the ODs (clusters). From the list of underserved ODs in Cambodia provided by CENAT, we will randomly allocate four ODs with high TB incidence and four ODs with low TB incidence to the intervention and control arms, matched by the population size and the number of health centers.

#### Concealment mechanism

Randomization will be performed by a person who will not be otherwise engaged in the project and will be blinded to the identity of the districts. Project coordinators and residents in the selected ODs will not be masked to the intervention. All case-finding activities share the same objective—to find TB cases—and they will be done without reference to the intervention group.

#### Implementation

The population living in the selected ODs will be included in the respective cluster. There will be four arms (Fig. 1), and two clusters will be randomly allocated to each arm. As all interventions have been endorsed by the CENAT and conducted in Cambodia, participants will not be notified if they are part of the intervention or the control group.

### Assignment of interventions: blinding

#### Who will be blinded

The data analysts will be masked to intervention allocation and will only analyze de-identified data.

#### Procedure for unblinding if needed

This pragmatic cluster randomized trial is open-label, where project coordinators and staff are not blinded. All case-finding activities will be implemented in the selected sites, as indicated. Study participants and health center/laboratory staff will not be notified if they are part of the intervention group or the control group. Therefore, unblinding will not occur in this trial.

### Data collection and management

#### Plans for assessment and collection of outcomes

For the primary endpoints, we will collect case notification data from the intervention implementers (CATA, KHANA, CENAT), the provincial health department, and health centers (Table 2). For the secondary endpoints, data on treatment outcomes will be collected from the health centers. To assess the number needed to screen, we will collect screening data and the number of TB cases diagnosed from the intervention implementers, the provincial health department, and health centers. Data on costs—direct and indirect medical costs [29, 30], intervention, diagnostics, and medications—will be collected from the intervention implementers and the baseline and follow-up surveys (Table 2). In the survey, we will document the baseline characteristics of new diagnoses found in all arms using a questionnaire. Information on age, gender, education level, occupation, number of family members and housing, smoking, alcohol use, drug use, TB history, and the presence of other comorbidities will be collected. We will adapt and contextualize the knowledge, attitude, and practice survey instrument tools developed by the WHO to collect information on TB knowledge, attitudes, and care-seeking behavior toward TB [31]. A short follow-up survey will be conducted at the end of the TB treatment period for each person with TB to collect information on missed doses, side effects, and other TB treatment-related costs incurred.

**Table 2 Tab2:** Endpoints and data collection

Study endpoint	Description	Data source
Primary endpoints		
Case notification rates (cases notified per 10,000 population per year)	Numerator: number of cases notified by the selected districts	Case notification data from CENAT
	Denominator: total population in the OD	Population statistics (Ministry of Planning/Department of Statistics/CENAT)
Additionality (additional number of cases reported compared to historical baseline)	Number of cases notified by the selected districts	Case notification data from CENAT
	Historical data (cases notified in the preceding 3 years)	Historical case notification data from CENAT
Cumulative yield (cases diagnosed per 1000 screened)	Numerator: number of cases reported by each arm	Program data In the control arm, data to be collected from the health centers monthly
	Denominator: total number of individuals screened	Program data Provincial health department laboratory data to determine the number of people screened at health centers in the control arm
Secondary endpoints		
Treatment outcomes	TB treatment outcomes of all new patients 6 months after treatment initiation	Health centers
Number needed to screen	Numerator: total number of individuals screened	Program data Provincial health department laboratory data to determine the number of people screened at health centers in the control arm
	Denominator: number of cases reported by each arm	Program data Control arm: data to be collected from the health centers monthly
Cost per TB case diagnosed/notified	Direct and indirect medical costs while seeking care for TB Staff and intervention costs Diagnostics and medication costs	Health-care-seeking costs: data to be collected in the baseline and follow-up survey Intervention costs: data to be collected from KHANA, CENAT, and CATA DALYs: data to be extracted from WHO global burden of disease studies and other existing literature
Incremental cost-effectiveness ratio per DALY averted		

*CATA* Cambodia Anti-Tuberculosis Association, *CENAT* National Center for Tuberculosis and Leprosy Control, *DALY* disability-adjusted life year, *OD* operational district, *TB* tuberculosis, *WHO* World Health Organization

Data collectors (project staff from CATA, CENAT, KHANA, and/or health center staff) will be trained to explain the study to the participants, obtain written consent for the surveys (Additional file 2), and administer the questionnaire. The data collectors will brief participants on the nature and purposes of the study and potential risks, and will highlight that information will be kept confidential. Consent for the surveys will be taken by the data collectors in a private space after randomization.

Data collectors will administer the questionnaire (both questionnaire 1—baseline survey and questionnaire 2—follow-up survey) on-site using a tablet-administered format. The baseline survey will take between 30 and 40 min to complete, and the follow-up survey will take approximately 30 min to complete. The surveys may be conducted via telephone calls for participants who are unable to visit the health centers for interviews. Refusals will be excluded from this study, but consent will be sought to record demographic characteristics (participants would only be completing the “Socio-Demographics” section of the questionnaire if they have signed the Consent Form indicating consent to participate in the study but later choose not to complete the questionnaire). Participants will be reimbursed USD 2 for their participation at baseline (questionnaire 1) and USD 2 for an exit interview (questionnaire 2) at the end of the 6-month follow-up.

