### Interventions

#### Explanation for the choice of comparators

The PCF strategy is a default setup in the national health system. PCF is a patient-initiated pathway that relies on the self-presentation of presumptive TB cases to the health centers to be diagnosed with TB. Upon screening by health center staff, sputum samples from presumptive TB cases belonging to the KAPs will be collected for examination by GeneXpert or direct smear microscopy if the GeneXpert system is not available. CXR will be performed at the referral hospital if the sputum examination result is negative. TB diagnoses will be made by clinicians based on clinical, radiological, and microbiological evidence. For presumptive TB individuals who present with cough for less than 2 weeks, CXR will be performed at the referral hospital, and sputum samples will be collected for GeneXpert testing if radiological abnormalities are detected [23]. For presumptive TB cases who do not belong to KAPs, smear examination will be performed if presenting with a cough lasting for 2 weeks or more. Those presenting to the health centers with cough for less than 2 weeks will be referred to the referral hospital for CXR, and cases with any radiological abnormalities will undergo smear examination [23]. Newly diagnosed people with TB will be treated and managed according to the national TB guidelines. We will follow-up all people with TB diagnosed during the study period for 6 months from the treatment initiation.

This is a patient-initiated pathway to TB diagnosis involving: a person with active TB experiencing symptoms that he or she recognizes as serious; a person having access to and seeking care, and presenting spontaneously at an appropriate health facility; a health worker correctly assessing that the person fulfills the criteria for presumptive TB; and the successful use of a diagnostic algorithm with sufficient sensitivity and specificity to diagnose TB.

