**Fig. 2 Fig2:**
[figure not shown]
Active case finding with a seed-and-recruit model. A network is built by seed, as illustrated by the dotted lines in the left panel. The network is expanded in a snowball fashion by recruiters who will be trained to recruit other people who might have tuberculosis (TB) in the community. We refer key populations for TB in this study to people aged 55 and above, people with diabetes, people living with HIV, household contacts of TB patients, and people who use and inject drugs. For GeneXpert test, one sputum specimen will be collected. For smear microscopy, three sputum specimens will be collected at three different times, over 2 days

All presumptive TB cases referred by seeds and recruiters will be screened by lay counselors using a symptoms screening questionnaire [17]. The screening for symptoms compatible with TB includes a cough lasting for at least 2 weeks, hemoptysis, fever, weight loss, and night sweats [17]. Presumptive TB cases and their symptoms screening questionnaire will be assessed by a nurse practitioner in the health center for further TB work-up. Those who are presumed to have TB will be asked to submit sputum samples at the health center for acid-fast bacilli examination. Sputum samples of KAPs will be assessed using the GeneXpert system at the referral hospital laboratory. For non-KAPs, direct smear microscopy will be undertaken at the nearest laboratory. If the sputum examination results are negative, further assessments and diagnosis of TB will be made on clinical and radiological grounds by clinicians. TB screening and treatment will be provided at the health facilities at no cost to the patient, in accordance with the policies of the NTP. Cases suspected of extrapulmonary TB (presence of local and general symptoms [23]) will be referred to the OD referral hospital for further assessment and diagnosis. We will follow-up all people with TB referred by seeds for 6 months from the treatment initiation.

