For the secondary endpoints, we will evaluate the treatment outcome of TB cases detected in this study according to the following categories: treatment completed (without evidence of failure); treatment failed (sputum smear remains positive at month 5 or later of treatment); died (death due to any reasons before and during treatment); lost to follow-up (people newly diagnosed with TB who do not initiate treatment or treatment course that is disrupted for 2 or more successive months); not evaluated (no treatment outcome data available); and cured (sputum smear converted from positive to negative in the final month of the treatment and on at least one earlier assessment at month 2 or month 5) [23]. The number needed to screen to detect one TB case in each arm will be calculated by dividing the total number of persons screened by the number of TB cases detected (i.e., the reciprocal of the absolute cumulative yield). Direct and indirect medical costs that will be incurred before and during health-seeking will be measured based upon the baseline and follow-up questionnaires. Costs for identification of presumptive TB cases and engagement with KAPs for screening, including training and meetings before initiating ACF activities, will be categorized separately from the costs for diagnosis using radiological/bacteriological means and management of people with TB. The incremental cost-effectiveness ratio (ICER) will be estimated by dividing the difference in total costs between trial arms by the difference in the total number of TB cases detected. The ICER per disability-adjusted life year averted will also be considered as a benchmark to determine whether the interventions are cost-effective.

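### Cumulative yield and number needed to screen count people at the laboratory in control but at an earlier step in the ACF arms, so they cannot be compared with control as defined

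*Protocol article*

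**What the plan says.** **Status of the endpoint.** The abstract and Table 2 of the protocol article list cumulative yield as primary, and *Statistical methods for primary and secondary outcomes* treats it so. *Outcomes* names only the case notification rate as the primary endpoint and introduces yield as something determined in addition. *Outcomes* also says that the endpoints are measured in all four arms.

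**Denominator.** For yield and NNS, Table 2 takes the number screened from program data. For control it adds "Provincial health department laboratory data to determine the number of people screened at health centers in the control arm".

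**Numerator.** Table 2 heads the endpoint "Cumulative yield (cases diagnosed per 1000 screened" and takes as numerator the cases reported by each arm (control: from health centers, monthly). *Statistical methods* instead describes "dividing the number of cases notified in each arm by the total number of people screened for TB". For NNS it divides by cases detected and calls the result "the reciprocal of the absolute cumulative yield".

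**Pathways.** In control, under *Explanation for the choice of comparators*: "Upon screening by health center staff, sputum samples from presumptive TB cases belonging to the KAPs will be collected for examination by GeneXpert". For people outside the key affected populations with a shorter cough, X-ray comes first, and only "cases with any radiological abnormalities will undergo smear examination". In the seed-and-recruit arm: "All presumptive TB cases referred by seeds and recruiters will be screened by lay counselors using a symptoms screening questionnaire". In the mobile-unit arm: "Each person who visits the screening session will be screened and surveyed at registration by trained staff".

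**The concern.** Yield is cases over people screened, so an arm's result depends on where counting starts. If control is counted at the laboratory, people who were screened but never tested drop out of its denominator. If the ACF arms are counted at the symptom screen or at registration, the same kind of person stays in. Control yield is then too high and control NNS too low relative to ACF, whatever the strategies achieve. A strategy that finds extra cases could appear inferior to passive case finding on a listed primary endpoint and on the NNS derived from it.

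This is not detail left for an analysis plan. Table 2 fixes the data source, and no later model can restore control screens that were not recorded.

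**Working it through.** The article gives no planned value for yield or NNS, so there is no figure to reproduce. The check compares the counting steps and then sizes the effect under stated assumptions.

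**1. Steps side by side**

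| Arm | Step described as screening | What leads to a laboratory test | Source of screened count |
|---|---|---|---|
| Control | Screening by health-center staff | Presumptive TB; with shorter cough, only after an abnormal X-ray | Laboratory data |
| Seed-and-recruit | Symptom questionnaire by lay counselor | Still presumed to have TB after nurse assessment | Program data |
| Household and neighborhood contacts | On-site symptom screen, with X-ray | Suggestive X-ray and/or symptoms | Program data |
| Mobile units | Every attender at registration | Suggestive X-ray | Program data |

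In every arm the described screening precedes the laboratory. Only control is counted at the laboratory.

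**2. Formula.** Let N people be screened and C cases found in each of two arms that perform identically, and let f be the share of screened control patients who appear in laboratory data.

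- ACF yield = 1000 × C / N; NNS = N / C
- Control yield = 1000 × C / (f × N); NNS = f × N / C
- Apparent ACF/control yield ratio = f
- True ratio that ACF needs to show parity = 1 / f

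**3. Numbers.** Assumed: N = 1000 and C = 20, so ACF yield is 20 per 1000 and NNS is 50. The article does not give f.

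| f | Control yield per 1000 | Control NNS | Apparent ACF/control ratio | True ratio needed for parity |
|---|---|---|---|---|
| 1.0 | 20 | 50 | 1.0 | 1.0 |
| 0.8 | 25 | 40 | 0.8 | 1.25 |
| 0.5 | 40 | 25 | 0.5 | 2.0 |
| 0.3 | 66.7 | 15 | 0.3 | 3.33 |
| 0.2 | 100 | 10 | 0.2 | 5.0 |
| 0.1 | 200 | 5 | 0.1 | 10 |

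**4. Which arm is most exposed.** The same arithmetic can be run from the ACF side. Assume 1000 attenders at mobile sessions, 200 tested and 20 cases: yield 20 per 1000, NNS 50. A control district that also tests 200 and finds 20 cases, but counts only those tested, shows 1000 × 20 / 200 = 100 per 1000, NNS 10. The ratio is 1000 / 200 = 5. With 10% to 50% of attenders tested, it runs from 10 down to 2. This example suits the mobile-unit arm, where asymptomatic people aged 55 or over are counted. In the seed arm the people screened are already referred as presumptive cases, and in the contact arm symptoms alone can lead to sputum testing. Most people counted there may be tested, so the gap may be small.

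**5. Numerator against denominator in control.** Control cases come from health centers, and *Outcomes* counts extrapulmonary TB defined by local and general symptoms. Such cases can enter the numerator with no laboratory record in the denominator, which raises control yield further. Smear-negative cases are less exposed, because their definition requires two negative samples.

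**The case against.** **The laboratory data may be only a proxy.** Their stated purpose is to establish how many people were screened, and the text before Table 2 names health centers among the sources of screening data. The article also never says which step the program counts use. This stands as uncertainty about size. It does not remove the problem: Table 2 assigns laboratory data to the control denominator and health-center data to control cases, and nothing shows that the program counts start at the laboratory.

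**Yield may not carry the trial.** *Outcomes* names one primary endpoint, the power simulations concern notified cases, and no specific test of yield against control is written down. This limits the damage. But the abstract and Table 2 make yield primary, and the planned analysis covers all primary and secondary endpoints.

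**The size is assumed.** Correct, and the five-fold example fits mainly one arm.

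**NNS as the reciprocal of yield** is openly stated. It is redundant, not an error.

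**A stronger reading.** Because *Statistical methods* says notified, a reader might infer that all district notifications are divided by program screens. The documents do not support this. Table 2 reserves district notifications for the notification rate and additionality, and pairs program cases with program screens for yield. Such a calculation would also favor ACF. If ACF supplied only the additional cases, its yield would be multiplied by (1 + E) / E, where E is the effect size in *Sample size*: 5.0 at 25%, 4.33 at 30%, 1.91 at 110%. Combined with f = 0.5, the apparent ratio would run from 0.5 × 5.0 = 2.5 to 0.5 × 1.91 = 0.95, so no fixed direction follows. What remains is conflicting wording: diagnosed or reported, notified, detected.

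**Conclusion.** The point holds for the denominator. As defined, yield and NNS compare a laboratory count in control with program counts whose described screening steps come earlier. On that account alone, control yield is overstated and control NNS understated relative to ACF.

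The apparent ratio is the true ratio multiplied by f. That factor could be near 1 or far below it, and the article gives nothing to fix it. The conclusion rests on two readings: that laboratory data record people who reached a test, and that program counts follow the screening steps described for each arm. Part of any low yield per attender in the mobile-unit arm would be a genuine property of screening asymptomatic people, but the present definitions cannot separate that from the counting rule.

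The numerator terms are a drafting conflict to reconcile, not evidence of a further bias. Case notification rate and additionality do not use this denominator.

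**What to change.** 1. In Table 2 and *Statistical methods for primary and secondary outcomes*, define one step counted the same way in all four arms, and take as numerator the cases arising among those same people.
2. If control can supply only persons tested, make any cross-arm comparison per person tested. State that triage before testing differs by arm (for example, a suggestive X-ray in the mobile-unit arm, mainly symptoms in control) and that cases diagnosed without a laboratory test are excluded from that ratio.
3. In that case, report yield and NNS per person screened descriptively for the ACF arms, without a test against control.
4. Use one numerator term throughout Table 2 and *Statistical methods*, and make yield's status in *Outcomes* agree with the abstract and Table 2.

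The cost is some extra tabulation from testing records and a narrower claim for yield. The article does not say that the programs hold counts of persons tested, so this needs confirming first; seed-arm GeneXpert tests, for example, are run at the referral hospital laboratory.
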